### Inflammatory/antimicrobial markers and short chain fatty acids (SCFAs) analysis

4.5

Faecal samples will be analysed for calprotectin (kit Calprest NG, Eurospital, with an adaptation on BEP2000 (Siemens)), β-defensin 2 (β Defensin 2 ELISA Kit, Immundiagnostik, Bensheim), and HNP1-3 (human HNP1-3 ELISA Kit, Hycult biotech). All 3 markers will be measured in the Laboratory of Functional Coprologie, GH Pitié-Salpêtrière, Paris. The C-reactive protein will be measured in plasma by CRP human ELISA kit (Enzo Life Sciences). The SCFA concentration will be dosed after water extraction of acidified faecal samples using gas liquid chromatography (Nelson 1020, Perkin-Elmer) in the Commensals and Probiotics-Host Interactions Laboratory, Micalis Institute, INRA UMR 1319, France.

### DNA extraction

4.6

A DNA extraction on all samples will be performed in batches to reduce the possibility of manipulation errors between extractions.

#### Sample pre-treatment

4.6.1

**Lung tissue.** Lung tissue will be taken directly from liquid nitrogen, broken into smaller pieces with a mortar and pestle, and homogenised in Hank's balanced salt solution (HBSS) (Sigma-Aldrich) in gentleMACS M tubes (Miltenyi Biotec). The ratio of buffer volume:sample weight will be determined for each sample, and adapted volume will be used for each of the following steps. The programs used will be those adapted for lung and tumour tissue (Miltenyi Biotec). The homogenate obtained will be treated with collagenase D (Sigma-Aldrich) (2 mg/mL final concentration) at 37°C for 15 min, followed by 10 min at 2000 × g at room temperature (RT). The pellet will be resuspended in 2–5 mL (depending on the initial sample weight) of mammalian cell lysis buffer (MCLB),^[24]^ and repeatedly vortexed for 5 min at RT. The reaction will be stopped with adding an equal volume of neutralisation buffer.^[24]^ After 2 washes with PBS (Sigma) (2000 × g for 10 min), the pellet will be used for DNA extraction using the adapted protocol of Godon et al.^[25]^

**Saliva and BALF.** Saliva and BALF will first be brought to RT and vortexed. 1 mL of saliva and 5 mL of BALF will be used for DNA extraction. Whole BALF will be used for extraction, to minimise the loss of bacterial communities.^[26]^ BALF will be centrifuged (7000 × g, 10 min) and 3 mL of MCLB will be added to the pellet, while saliva will be treated directly with 1 mL of MCLB. Both will be vortexed for 5 min at RT, followed by addition of neutralisation buffer. DNA extraction will be performed directly on the pellet after centrifugation at 7000 × g for 10 min at RT and a washing step (PBS).

**Faeces.** Faecal samples will have no pre-treatment and extraction will begin directly on frozen samples.

#### DNA extraction

4.6.2

DNA extraction will be performed by using the adapted protocol of Godon et al.,^[25]^ i.e. International Human Microbiome Standards Standard Operating Protocol for Fecal Samples (IHMS SOP) 07 V1. Briefly, 4 M guanidine thiocyanate and 10% N-lauroyl sarcosine will be added directly on frozen samples or pellets for 10 min at RT. After the addition of 5% N-lauroyl sarcosine and homogenisation by vortexing, the samples will be incubated for 1 h at 70°C. All of the samples will be transferred to Lysing Matrix B tubes (MPBio) and homogenised using FastPrep-24 Instrument (MPBio), 4 × 45 s at 6.5 ms^−1^. Between each cycle, the samples will be cooled on ice for 2 min. One micro-spoon of polyvinylpolypyrrolidone will be added to each tube, followed by vortexing and centrifugation for 3 min at 18,000 × g. The supernatant will be removed and placed in a new 2 mL tube and the pellet will be washed with TENP and centrifuged for 3 min at 18,000 × g, and the new supernatant will be added to that which was harvested previously. The pooled tube will be centrifuged for 1 min at 18,000 × g and the supernatant will be transferred to a new 2 mL tube. One volume of isopropanol will be added to the supernatant, gently mixed by turning the tube and incubated for 10 min at RT. After centrifugation for 5 min at 18,000 × g, the pellet will be resuspended in 0.1 M phosphate buffer, pH 8, and 5 M potassium acetate and incubated overnight at 4°C. The samples will then be centrifuged for 30 min at 18,000 × g and 4°C. The supernatant will be transferred to a new 2 mL tube, and after the addition of RNase (final concentration 40 μg/mL), incubated at 37°C for 30 min. Nucleic acids will be precipitated with absolute ethanol and 3 M sodium acetate, followed by centrifugation at maximum speed for 3 min. The pellet will be washed with 70% ethanol, dried and resuspended in 100 μL of TE buffer. DNA quality and concentration will be estimated by agarose gel electrophoresis and nanodrop (NanoDrop ND-1000) measurement, respectively.

Considering the low biomass samples, background controls have been made throughout the sampling and extraction process. The physiological serum used to perform BAL is 1st sampled with the same syringe that is afterward used for lavage from the same vessel containing physiological serum. This sample is used as a “negative sampling control”. During the DNA extraction, miliQ water is used as a “negative background control” sample, treated will all the reagents and passing all the procedures along with the real samples. These “negative” samples will be analysed along with the real samples.

All the reagents used in DNA extraction and sample pre-treatments were either autoclaved, filtered through 20 μm filters or purchased sterile. All the tools and pipettes were thoroughly washed and disinfected between extractions of different sample types, to minimise the transfer from high biomass samples. Also, DNA extraction from lung tissue samples (3 samples per patient) was randomised (each extraction “batch” never contained only one sample type from different patients or all the samples from the same patient), to minimise the “batch” effect.

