The strong point of this trial is that study participation does not modify the patient's standard care treatment in any way. Invasive intervention, such as sampling of the lung tissue, is done during operation on the lung already removed from the patient. The BALF sampling during operation is performed directly on the dissected lobe, posing no additional inconvenience for the patient and drastically minimising UAs contamination, which is an important advantage to this study's concept. Likewise, sampling of the BALF at CT1 for group Pct-chir is done in the scope of a standard care procedure by bronchoscopy and it is not imposed by the study. However, the latter is also an inconvenience because there will be patients from group Pct-chir who will not undergo bronchoscopy with BALF sampling since it is not prescribed by his/her physician. Another thing to consider is also the difference in sampling technique of BALF. Sampling of BALF at CT1 for group Pct-chir is done by bronchoscopy, while sampling during surgery is done directly on the excised lobe for both groups. Therefore, the 1t BALF has a higher risk of contamination by UAs, while the 2nd BALF (during operation) should have no UAs contamination and better represent luminal microbiota specific of the tumour lobe. This will be taken into account during data interpretation, and if necessary, each time point will be characterised for itself.

In conclusion, in the group Pct-chir, the effect of chemotherapy on the microbiota of saliva and faeces and immune parameters of blood and faeces will by systematically assessed. Chemotherapy's effect on immune parameters and microbiota in BALF will be assessed only if obtained data in quantity and quality will permit it (as explained above). When talking of lung tissue, “healthy” lung tissue, taken at distance from the tumour, will be considered as a control^[12]^ tissue for comparison with peritumoural and tumoural tissue, as well as with BALF. Also, characterisation will be done respective to the tumour type where possible (sufficient patient number with the same tumour type).

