#### The 16S rRNA gene sequencing

4.7.1

The genomic DNA from saliva, faeces, BALF, “healthy” lung, peritumoural and tumoural tissue, and negative controls will be analysed by sequencing of the bacterial 16S rRNA gene by DNAVision, Belgium, using Illumina MiSeq technology. After PCR amplification of the targeted region V3–V4, libraries will be indexed using the NEXTERA XT Index kit V2. The sequencing is carried out in paired-end sequencing (2 × 250 bp) by targeting an average of 10,000 reads per sample. Software used for bioinformatic analysis will be QIIME (Quantitative Insights Into Microbial Ecology), with a cut-off value of 5000 reads per sample for analysis. For each sample the following will be determined:

a)alpha and beta diversity,b)comparison of alpha diversities based on a 2-sample *t* test using non-parametric (Monte Carlo) method,c)statistical significance of sample groupings using distance matrices (Adonis method),d)comparison of OTU frequencies across sample groups (comparison is performed at OTU, Phylum, Class, Order, Family and Genus level)

Multiple comparisons will be realised, both between different grouping criteria and between samples.

Considering the low taxonomic levels (Species), sequencing is best used as an indicative tool for further analyses by qPCR.

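### Lung-tissue extraction is spread over batches but no named analysis includes batch, and the 5,000-read cut-off carries no exemption for the negative controls

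*Protocol article*

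**What the plan says.** **Batches.** Section 4.6.2 states that "DNA extraction from lung tissue samples (3 samples per patient) was randomised" and that a batch "never contained only one sample type from different patients or all the samples from the same patient", the aim being "to minimise the “batch” effect". Section 2.5 makes the tissue contrast a within-patient one: healthy lung, "taken at distance from the tumour, will be considered as a control" for peritumoural and tumour tissue.

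**Analyses.** Section 4.7.1 names a Monte Carlo t test for alpha diversity and Adonis for distance matrices. Section 4.8.4 names ANOVA. Section 4.8.5 names a mixed model that adjusts for patient and phylum. Batch appears in none of them.

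**Blanks.** Section 4.6.2 describes two kinds of negative control, lavage saline and water carried through extraction, and says: "These “negative” samples will be analysed along with the real samples". Section 4.7.1 confirms that "peritumoural and tumoural tissue, and negative controls will be analysed by sequencing of the bacterial 16S rRNA gene". The same paragraph gives a target average of 10,000 reads per sample and specifies QIIME "with a cut-off value of 5000 reads per sample for analysis". It does not say whether the cut-off covers the controls. No rule is given for what a finding in a blank does to the lung results.

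**The concern.** Comparing tissues from the same patient removes between-patient variation. If the tissues are extracted in different batches, batch-to-batch variation re-enters each difference. A factor used to lay out the laboratory work, and judged important enough to randomise over, would normally appear in the analysis. Here the article names its adjustment terms and batch is not among them.

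On the blanks, a control with little bacterial DNA is a natural candidate to miss a read threshold set at half the target average. Applied literally, the threshold can remove the controls whose purpose is to show background in low-biomass samples. Lung microbiota is part of the primary outcome (section 2.2). A reagent taxon listed as a lung taxon would be a wrong description, even in a purely descriptive study.

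**Working it through.** The plan gives no figure on batch or on reads in blanks, so there is none to reproduce. Its sample size of 20 per group rests on faecal *Firmicutes* and does not bear on this point.

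**Inputs from the article:** 3 lung tissues per patient; 40 patients, hence 3 × 40 = 120 tissues; randomised extraction; no batch term.

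**Assumptions:** batch size m = 6 to 24; r = batch variance ÷ within-patient residual variance = 0.25 to 1; all 120 tissues available.

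**Step 1: how many pairs cross batches.** If no batch holds all three tissues of a patient, they split 2+1 or 1+1+1, so at least 2 of the 3 pairs cross. The sentence can also be read with *only* governing both halves, so that no batch consisted solely of one patient's samples. Randomisation then still separates most pairs. The chance that a given pair shares a batch is (m − 1)/119, which is 5/119 = 4% for m = 6 and 23/119 = 19% for m = 24. About 81% to 96% of pairs cross. On the stricter reading, simulation with 20 or 40 patients and batches of 6 or 12 gave 83% to 96% for tumour–healthy pairs.

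**Step 2: variance of one difference.** With residual variance s²e and batch variance s²b, it is 2s²e if both tissues share a batch and 2(s²e + s²b) if not. Relative to no batch effect, a crossing pair has variance 1 + r, which is 1.25 at r = 0.25 and 2.00 at r = 1.

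**Step 3: what modelling batch recovers.** The useful comparison is with an analysis that includes batch, which removes most but not all of this variance. I computed the variance of the mean tumour–healthy difference for 40 patients, averaged over random layouts on the stricter reading. Patient effects were removed, and batch was either ignored or fitted as a random effect with known variance. The first two figures in each cell are relative to no batch effect; the last is their ratio.

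| Batch size | r = 0.25 | r = 0.5 | r = 1 |
|---|---|---|---|
| 6 | 1.23 / 1.13 = 1.09 | 1.48 / 1.19 = 1.24 | 1.97 / 1.24 = 1.59 |
| 12 | 1.22 / 1.08 = 1.13 | 1.47 / 1.10 = 1.33 | 1.97 / 1.12 = 1.75 |
| 24 | 1.20 / 1.04 = 1.15 | 1.38 / 1.04 = 1.32 | 1.77 / 1.05 = 1.69 |

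The looser reading, and 20 patients instead of 40, give the same range: about 1.1 to 1.7 in variance, or √1.1 = 1.05 to √1.7 = 1.30 in standard error.

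**Step 4: bias and type I error.** In simulations of the paired test ignoring batch (2,000 runs per setting, 20 or 40 patients, batches of 6 or 12), bias lay between −0.007 and 0.010 residual SD. Type I error was 0.044 to 0.062 against a nominal 0.05. The layout turns batch variation into noise, not into a false signal.

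**Step 5: blanks.** Set side by side, section 4.6.2 says the negatives are analysed with the real samples, while section 4.7.1 includes them in the sequenced set and then applies a threshold to each sample. For a blank under 5,000 reads the two statements cannot both be followed. The article gives no read distribution for controls, so the share affected cannot be calculated.

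**The case against.** The strongest reply is that this is a condensed article for an exploratory study. A batch covariate or a contaminant filter could sit in a fuller document, and the randomised layout is a strength. Much of that stands. Randomising keeps batch from being confounded with tissue type or patient. The tissue contrast is a secondary item, under concordance between locations in section 2.2. The mixed model of section 4.8.5 cannot concern lung tissue, which is taken only at surgery. What does not stand is that the article is merely silent: it has its own statistical section, names model terms there, and sets a numerical cut-off in the paragraph that lists the controls.

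A reader might go further and infer that the cut-off does drop the blanks, or that contaminants remain in the primary lung results. The documents show neither. No read counts for blanks are given, and the one statement about their use is that they are analysed. A reader might also try to project how many patients lose lung samples to the cut-off. That would need an assumed read distribution, and no named analysis requires every lung sample from a patient.

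It may also be said that qPCR (section 4.7.2) is free of the read cut-off. That is true, but its second phase quantifies taxa that sequencing has picked out, so a contaminant that passes sequencing can become a qPCR target.

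**Conclusion.** The point holds in two limited parts. First, omitting extraction batch from the lung-tissue comparisons costs precision: the variance is about 1.1 to 1.7 times that of an analysis with batch. This rests on assumed variance ratios of 0.25 to 1 and batches of 6 to 24, and it holds on either reading of the batch sentence. It would be wrong to infer that the results are biased or the tests invalid; the randomised layout protects against both. Second, the cut-off as worded can exclude low-read negative controls that another section says will be analysed, and nothing states how the controls inform the lung results. The size of this second part is unknown. Both are worth settling before the lung results are analysed. Neither undermines the design.

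**What to change.** 1. In the lung-tissue comparisons, fit extraction batch as a random effect crossed with patient.
2. In Adonis, enter batch as a covariate term. Do not use it as a permutation block: most of a patient's tissues lie in different batches, so permuting within batch would exchange labels between patients and break the pairing.
3. State that the 5,000-read cut-off does not apply to negative controls.
4. Use the controls to flag likely contaminant taxa, and report lung tissue and BALF results with and without those taxa.

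**Cost:** wording and some analysis time. Extraction was organised by batch and the blanks are already part of the procedure, so no new sampling is needed. A fixed batch term, as in Adonis, uses 4 degrees of freedom for batches of 24 (120/24 = 5 batches) and 19 for batches of 6 (120/6 = 20 batches), out of 120 − 40 − 2 = 78 within-patient. With small batches and little batch variation that can cost more than it gains, which is why the random effect is preferred where a model allows it. Some true low-abundance taxa may be flagged as contaminants; reporting both versions makes that visible.

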### Molecular analyses of microbiota

4.7

#### The 16S rRNA gene sequencing

4.7.1

The genomic DNA from saliva, faeces, BALF, “healthy” lung, peritumoural and tumoural tissue, and negative controls will be analysed by sequencing of the bacterial 16S rRNA gene by DNAVision, Belgium, using Illumina MiSeq technology. After PCR amplification of the targeted region V3–V4, libraries will be indexed using the NEXTERA XT Index kit V2. The sequencing is carried out in paired-end sequencing (2 × 250 bp) by targeting an average of 10,000 reads per sample. Software used for bioinformatic analysis will be QIIME (Quantitative Insights Into Microbial Ecology), with a cut-off value of 5000 reads per sample for analysis. For each sample the following will be determined:

a)alpha and beta diversity,b)comparison of alpha diversities based on a 2-sample *t* test using non-parametric (Monte Carlo) method,c)statistical significance of sample groupings using distance matrices (Adonis method),d)comparison of OTU frequencies across sample groups (comparison is performed at OTU, Phylum, Class, Order, Family and Genus level)

Multiple comparisons will be realised, both between different grouping criteria and between samples.

Considering the low taxonomic levels (Species), sequencing is best used as an indicative tool for further analyses by qPCR.

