
Therefore, to help to elucidate this new and extremely interesting field, we have decided to conduct a case-control observational study in patients with NSCLC. The study will include 2 groups of patients: 1st group Pchir, with patients eligible for treatment by surgery, and 2nd group Pct-chir, with patients eligible for a combined treatment consisting of neoadjuvant platinum-based chemotherapy followed by surgery.

The objectives of this study are:

(i)to characterise the gut, lung and upper airway microbiota in these patients;(ii)to evaluate the homogeneity/heterogeneity between different microbiota within the same subject/group of patients;(iii)to evaluate the impact of the microbiota composition on immune and inflammatory status of the patient (evaluated in the gut, blood, lung);(iv)to evaluate the effect of chemotherapy on the site-specific microbiota (UAs, lung, gut).

While group Pchir will have only 1 time point for sample collection, group Pct-chir will have multiple time points. The latter will enable follow-up on changes in microbiota and immune markers relative to the treatment progression.

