#### Sample size

4.8.2

The sample size calculation is based on the study of Montassier et al, 2015,^[53]^ where the abundance of the principal phylum *Firmicutes* in faecal microbiota decreased by approximately 30%, with an FDR-corrected *P*-value of .0002. Considering these results, 20 patients in the chemotherapy group should allow us to detect a similar variation in our samples, at least in the faecal microbiota. For group balance, the same sample size of 20 was retained for the surgery-only group.

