#### Description of microbiota

4.8.4

Microbiota characteristics consist in several hierarchical steps including:

Phylum: 4 main phyla are found in both lung and intestinal microbiota (*Firmicutes*, *Bacteroidetes, Actinobacteria*, and *Proteobacteria*). *Firmicutes* are supposed to represent ∼80% of the intestinal microbiota biomass^[54]^ and ∼40% of the lung microbiota.^[55]^ The proportion of each component will be described by its proportion of the biomass in %.Main classes of bacteria per phylum: these classes gather bacteria that share important characteristics and functions (e.g. *Bacilli*, *Clostridia*, *Gammaproteobacteria,* etc.). Composition of the microbial communities from different sites and originating from different conditions will be quantified (alpha and beta diversity, relative proportions).Inside classes, description by order, family and genus level will be performed when contributory on a biological plan.

Heterogeneity between microbiota will be studied. The comparison of proportions of phyla, or by other taxonomic level will be performed to evaluate if specific adaptation characterises the 3 microbiota and their components. The ANOVA will be used to perform inter-patient comparisons. The FDR correction will be applied when analyses are conducted within phyla.

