#### Complementary analyses

4.8.9

Complementary analyses will be performed if particular biological issues can be better described.

All statistical analyses will be performed using R-software version 3.5.0 or later (R-Project, GNU GPL). Tests will be 2-sided and the significance threshold is set at 0.05, after FDR correction where needed (as for the analyses concerning taxonomic ranks below phylum). Data may be missing due to possible loss of follow-up between inclusion and end of study. A description of the missing data and associated reasons will be given.

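### Sections 4.7.1 and 4.8.4 assign tests with no patient term to within-patient site contrasts, and the diversity tests in 4.7.1 do not match those in 4.8.5

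*Protocol article*

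**What the plan says.** Objective (ii) in the Introduction is "to evaluate the homogeneity/heterogeneity between different microbiota within the same subject/group of patients". Around surgery every patient supplies six sample types: saliva, faeces, BALF and three lung pieces (2.5, 3.5). Section 2.5 makes each patient's healthy lung the control tissue for peritumoural tissue, tumour and BALF.

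The tests are named in four places:

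- **4.7.1 (16S sequencing).** Alpha diversity: "comparison of alpha diversities based on a 2-sample *t* test using non-parametric (Monte Carlo) method". Beta diversity: "statistical significance of sample groupings using distance matrices (Adonis method". The section says these comparisons will be made across several grouping factors and from sample to sample. It names no pairing, patient term or restriction on permutations.
- **4.8.4 (Description of microbiota).** Heterogeneity among the three microbiota and their components is to be studied. The only test named is: "The ANOVA will be used to perform inter-patient comparisons".
- **4.8.5 (Before/after chemotherapy).** Run separately for each site: a mixed model adjusting on patient for the main phyla, and univariate paired tests below phylum, said to extend to alpha and beta diversity. Student t and Mann–Whitney U are the examples given.
- **4.8.6 (Between treatment groups).** The same tests, unpaired.

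The error rate is fixed in 4.8.9: "Tests will be 2-sided and the significance threshold is set at 0.05, after FDR correction where needed".

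**The concern.** Samples from one person share diet, smoking, tumour and host factors, so they are correlated. A 2-sample test, a one-way ANOVA or an Adonis with labels permuted freely over all samples treats them as unrelated. The error this causes depends on the comparison:

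- **Within-patient contrast** (healthy against peritumoural against tumour, saliva against BALF). Differences between patients stay in the error term. The test is too conservative and loses power.
- **Patient-level factor** (treatment group, smoking, tumour type) tested on several samples per patient. The sample count overstates the information, and the test is too liberal.

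The first case is the direct one. Site contrasts serve objective (ii), and the lung microbiota belongs to the primary outcome. Section 4.8.5 shows that the authors allowed for the patient over time; no section does so over sites. The second case arises only if samples are pooled. The results also have a use: by 4.7.2, sequencing decides which further taxa go on to qPCR.

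**Working it through.** **The plan's own figure.** The only sample-size statement (4.8.2) is that "20 patients in the chemotherapy group should allow us to detect a similar variation in our samples, at least in the faecal microbiota". It concerns the before/after contrast, which 4.8.5 treats as paired. It gives no SD and no power, so 20 cannot be reproduced. For orientation, a paired t test with n = 20 has 80% power for a standardised change of 0.66. No figure is given for site contrasts.

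**Inputs.** Two-sided alpha 0.05 (4.8.9); 20 + 20 patients (4.8.2); three lung pieces, or four lung samples with BALF (3.5). The intra-patient correlation ρ is not given, so 0.3, 0.5 and 0.7 are assumptions.

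**Step 1: site contrast analysed as independent.** The true standard error is √(1−ρ) times the one assumed, so the effective critical value rises to 1.96/√(1−ρ).

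- True error rate = 2[1 − Φ(1.96/√(1−ρ))]
- Power kept, where the paired test has 80% = 1 − Φ(1.96/√(1−ρ) − (1.96 + 0.84))

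| ρ | Critical value | True error | Minus 2.80 | Power kept |
|---|---|---|---|---|
| 0.3 | 2.34 | 1.9% | −0.46 | 68% |
| 0.5 | 2.77 | 0.6% | −0.03 | 51% |
| 0.7 | 3.58 | 0.04% | 0.78 | 22% |

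At ρ = 0.8 about 6% is left. A simulation of three sites in 40 patients gives the same pattern: patient-blocked ANOVA has 83–84% power at every ρ, one-way ANOVA 69%, 49% and 16% at ρ = 0.3, 0.5 and 0.7.

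**Step 2: the same contrast by Adonis.** Simulated with two samples per patient, 20 patients, 10 independent equally correlated features, Euclidean distance and 199 permutations. Permuting within patient gives 85–86% power; free permutation gives 58%, 20% and 1% at ρ = 0.3, 0.5 and 0.7. With no true effect, within-patient permutation rejects 3–6%.

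**Step 3: patient-level factor with m samples per patient pooled.** The variance is inflated by 1 + (m−1)ρ, so the true error = 2[1 − Φ(1.96/√(1+(m−1)ρ))]. For m = 3:

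- ρ = 0.3: 1.96/√1.6 = 1.55, error 12%
- ρ = 0.5: 1.96/√2.0 = 1.39, error 17%
- ρ = 0.7: 1.96/√2.4 = 1.27, error 21%

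For m = 4 the rates are 16%, 22% and 27%. Simulated t tests agree within about 1 point. Free-permutation Adonis, with the same feature structure in 40 patients, rejects 34%, 52% and 63% for m = 3, and 48%, 70% and 86% for m = 4. With m = 1 the inflation factor is 1 and the error is 5%.

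**Step 4: 4.7.1 beside 4.8.5.** Both cover diversity. For alpha diversity one names a 2-sample test, the other paired tests. For beta diversity one names Adonis, a multivariate permutation test, the other univariate paired tests, which cannot deliver it. How Adonis would respect pairing is not stated. Mann–Whitney U is a two-independent-samples test and does not belong under paired tests.

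**The case against.** **Time contrasts are already handled.** A reader might infer that before/after comparisons ignore the patient too. The document does not support that: 4.8.5 specifies a patient-adjusted mixed model and paired tests. What remains for time is the mismatch in Step 4.

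**Pooling is not stated.** This stands in full. No section says lung pieces are pooled in a group comparison; 2.2 and 2.5 treat them as distinct sample types, and 4.8.5 and 4.8.6 work by site. A reader might infer that between-group tests are generally inflated. They are not: one sample type at one time point gives one value per patient, and the unpaired test is correct. Still, 4.8.1 and 4.8.4 speak of the lung as one microbiota, it comprises four samples per patient, and no rule excludes pooling. Step 3 is therefore conditional.

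**The ANOVA wording is ambiguous.** It is said to be for inter-patient comparisons, and 4.8.5 uses the word ANOVA for a mixed model. But if this ANOVA covers sites, no patient term is stated; if it does not, 4.8.4 names no test for the within-patient comparison.

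**Permutation strata belong in a full analysis plan.** Fair for Adonis taken alone. It does not cover a named 2-sample test or a misnamed paired test, which are choices the article states.

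**Power is not lost altogether.** A reader might infer that site contrasts have almost no power. For univariate tests that needs ρ of about 0.8 or more, and for free-permutation Adonis about 0.7 or more. Large contrasts could survive: 4.8.4 puts *Firmicutes* at about "80% of the intestinal microbiota biomass" and about 40% of the lung microbiota. Contrasts among neighbouring lung pieces may be smaller, and there the loss would matter more.

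**The study is exploratory.** Section 4.8.1 says so and calls the with/without-chemotherapy comparison descriptive. This lowers the severity, but a 0.05 threshold is still set and needs valid p-values.

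**Conclusion.** The point holds for site contrasts. Sections 4.7.1 and 4.8.4 name tests without a patient term for comparisons that the design makes within-patient, and no other section pairs them. The result is a conservative test that keeps roughly 68% to 22% power, where a paired analysis would have 80%, for ρ between 0.3 and 0.7; free-permutation Adonis loses more. Inflated false positives, 12% to 21% for a t test on three pieces, follow only if several samples per patient enter one test of a patient-level factor, which the plan neither states nor excludes. For time contrasts the defect is limited to conflicting and misnamed diversity tests.

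Every rate depends on an assumed ρ, and the Adonis rates also on the assumed feature structure. They show direction and rough size; they are not forecasts. Severity is moderate.

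**What to change.** - **Sites (4.7.1, 4.8.4).** State that comparisons between sample types, including healthy/peritumoural/tumour, use a mixed model with a random patient effect or a paired test for alpha diversity and taxa, and Adonis with permutations restricted within patient for beta diversity. Say what the inter-patient ANOVA is for.
- **Patient-level factors (4.7.1, 4.8.6).** Test group, smoking and tumour type on one sample type at one time point, or permute whole patients when several samples are used.
- **Time (4.7.1 with 4.8.5).** Name one set of diversity tests. Specify Adonis permuted within patient for beta diversity, and replace Mann–Whitney U by the Wilcoxon signed-rank test in the list of paired tests.

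The cost is a few sentences and a permutation-block option in the R routine. No additional patients, samples or sequencing are needed.
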